### Process evaluation

First, to enrich the outcome data collected in the RCT by understanding the context in which the outcomes developed, we will conduct a parallel process evaluation featuring individual qualitative semi-guided interviews with patients, GPs, practice staff, and MHS [77]. Participants will be sampled purposefully according to characteristics anticipated to influence implementation and outcomes. We will focus the interviews on barriers and facilitators for implementing the model. Applying a during-trial design nested in the RCT, we will collect process data at the various stages of the intervention, that is, early in the course of the intervention, during the intervention and after the intervention [78]. Specifically, we will use the domains (1) quality of implementation, (2) causal mechanisms/pathways, and (3) contextual influences on the implementation of the intervention as main top-down themes for thematic analysis of the interview data. We will also use the findings from the feasibility trial to inform the process evaluation. Coders conducting the qualitative analysis will not be involved in the delivery of the intervention and analyse the qualitative data prior to knowing the trial outcomes. Second, we will provide detailed information on participant retention per video consultation (e.g. average number of completed video consultations, number of participants who were allocated to the intervention but never started the video consultations). Finally, as part of a pre–post-study measurement of intervention implementability, all practice teams and MHS will fill in the Normalisation MeAsure Development (NoMAD) questionnaire prior to inclusion of the first patient and close-out of the last patient [79]. Specifically, the NoMAD assesses health professionals’ perceptions of factors relevant to embedding interventions that change their work practices.

### Retention

We will continuously monitor the trial for any operational issues (i.e. failure in appointment management, no-show of patients) by timely and directly communicating with the enrolled practices. Concerning data collection, we will prioritise short questionnaires to reduce participant burden. To encourage retention at each study timepoint, nonresponders will receive up to five reminders in total via phone, mail, and e-mail. For the baseline survey, these reminders will also provide the option of completing the assessment over the phone. For the 6- and 12-month survey, these reminders will offer the option of being mailed a hard copy of the questionnaire to complete and return via reply paid envelope and/or filling in the PHQ-ADS alone. Outcome assessments may be completed in multiple sittings.

### Data management

We will enter data from mail survey (baseline) and CATIs (6- and 12-month survey) on the password-protected online survey tool (Enterprise Feedback Suite (EFS) Survey, Questback GmbH) and enforce data integrity using forced or multiple-choice items wherever possible. A member of the research team will regularly check all data to identify and, where possible, resolve errors prior to analyses being conducted (e.g. by conducting range and plausibility checks). Data preparation prior to the main analysis will be conducted by two members of the research team independently. We will keep all data for 10 years after study completion after which time they will be destroyed in accordance with the recommendations of the Medical Faculty of the University of Heidelberg Ethics Committee. All computers and servers used to manage contact with participants and track progress through the study will be password-protected and housed in a secure environment at Heidelberg University; only the study team will have access to the identified data.

### Statistical methods

Descriptive statistics (absolute and relative frequencies for variables with nominal and measures of position (mean, median) and variability measures (standard deviation, interquartile range, and range) for variables with interval or ratio scaling) will be used to compare participant characteristics between the study arms.

For the analysis of the primary outcome, we will use the complete and pseudonymized data set and follow the intention-to-treat approach which includes all patients in the group they were allocated to by randomisation. In a sensitivity analysis, we will evaluate the per-protocol population in which only patients who will have participated in at least three video consultations (defined as engagement in video consultations) will be included. The null hypothesis for the primary outcome is: The absolute change in depressive and anxiety symptom severity from baseline to post assessment (6 months after baseline assessment) is the same in both groups. Provided that the model assumptions are fulfilled, the null hypothesis will be tested using a (robust) mixed linear regression model at a significance level of 5% [80]. In addition to the group variable, the regression model will contain the following variables at baseline: depressive and anxiety symptom severity, history of depression/anxiety, physical health status, chronic medical disease, gender, age (fixed effects), and trial site (general practice) (random effect). We will compute effect sizes and interpret them together with the respective 95% confidence intervals [81]. The analyses of the secondary outcomes will be purely exploratory and analogous to the analysis of the primary outcome. We will conduct subgroup analyses with respect to equality of the subgroups for the main and secondary objective criteria applying (robust) mixed linear regression models, which will also contain an interaction term between the study arm (intervention vs. comparison) and the subgroup to be investigated. The corresponding *p* values of these tests will be interpreted purely descriptively. If subjects discontinue the study, they will be described separately to provide clues as to possible selectivity. The entire statistical evaluation will be performed in R (version 4.0.5 or higher) [82]. Prior to all analyses, we will pre-specify a statistical analysis plan.

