The research group PROVIDE (ImPROving cross-sectoral collaboration between primary and psychosocial care: An implementation study on VIDEo consultations, https://www.provide-project.de/ziel-konzept/?lang=en), funded by the German Federal Ministry of Education and Research, focuses on innovative modes for delivering primary care mental health. To explore whether and how mental health specialist video consultations (MHSVC) can be implemented in routine primary care in Germany, i.e. a prototype single-handed practitioner system in particular, we conducted a randomised feasibility trial (PROVIDE-B) enrolling 50 patients with depression and/or anxiety between February and October 2019 [39]. In this feasibility trial, acceptability of MHSVC in terms of treatment retention (87.0%) and attendance at sessions (94.4%) was high. Moreover, the nested qualitative study showed that satisfaction was high both in patients and health professionals [40]. Study procedures, e.g. inclusion process, data collection, study monitoring, and appointment management proved to be feasible. Therefore, as the next step, a sufficiently powered randomised controlled effectiveness trial was planned.

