#### Comparison arm

Patients allocated to the control group will get the usual care provided by the GP. This may or may not include a referral to an MHS. We expect that most people with depression and/or anxiety disorders are currently treated by their GP only. GPs tend to provide brief counselling and prescribe psychotropic medication rather than conduct psychotherapy as laid out in guidelines [14, 55, 56]. Only every fifth patient with depression is referred to specialised care [4]. There will be no restrictions to the usual treatment by the GP.

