#### Intervention integrity

We formulated the following core intervention components [57]: (1) video consultations by mental health specialists, (2) specialist diagnostics, (3) fixed dose of five video consultations of 50 min each for each patient over a period of approximately 8 weeks, (4) interventions focus primarily on affect expression and regulation, and (5) specialist supervision [58–60]. Concerning intervention integrity, we consider criterion (1) as fulfilled through the recruitment of MHS, criterion (2) as fulfilled if the general practice has received a standardised diagnostic report after the 2nd video consultation, criterion (3) as fulfilled if the number of video consultations in the intervention log encounters kept in trial coordination centre corresponds with the prespecified default, and criterion (5) as fulfilled if the number of supervisions sessions in the log encounters corresponds with the prespecified default. We will assess the adherence to criterion (4) by requesting the therapists to fill in an online self-assessment questionnaire at the end of each video consultation. Notwithstanding, we will continuously monitor and foster intervention integrity, e.g. by reviewing treatment progress in the regular supervision. However, we consider this study as a pragmatic trial in a real-world service setting, so that—as part of local modifications/adaptions—the MHS are not expected to follow the manual exactly but may work according to their own judgement of what fits with patient characteristics to some extent [61]. In the control arm, to compare usual care before and during participation in the trial, information about health service use will be collected at each study assessment.

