A major methodological consideration for the PROVIDE-C trial was weighing an individually randomised design vs. a cluster-randomised design. Randomising individuals who are recruited from the identical general practice, where the GP is not masked to the participant’s study arm, may bear a greater risk of contamination between arms than randomising a group of individuals that do not belong to the same practice. While we did consider designing a cluster-randomised trial, we eventually opted for an individually randomised trial. Specifically, we decided to proceed in this way for several reasons: First, while the GP will recruit individuals, she or he will not be involved in delivering the intervention and will have no access to the allocation schedule. We consider this as an advantage over cluster-randomised trials which are associated with a significant risk of recruitment bias. Second, we applied a recently developed framework for identifying the risk of contamination [93]. The framework accounts for three possible sources of contamination: (a) participants in the control arm, (b) participants in the intervention arm, and (c) therapists in the intervention arm. In sum, considering all three sources, we consider the overall risk of contamination in the PROVIDE-C trial low. Third, prior work shows that in therapy trials risk of contamination occurs rarely and is generally low across trials [93]. Notwithstanding, current evidence supports the decision to choose an individually randomised controlled trial rather than a cluster-randomised trial based on the observation that the latter designs are only more efficient when contamination exceeds 30% [94, 95]. Fourth, considering the potential drawbacks of implementing cluster-randomised trials in terms of ethical issues, the need for a larger sample size, and recruitment bias, recent recommendations promote individually randomised trials when the intervention accessibility (timely video consultations with mental health specialists are not available in routine primary care in Germany and can only be accessed by permission of the study team) is limited and complex to deliver (we used highly trained mental health specialists who delivered a multi-component manual-based intervention and had no contact at all with participants from the control arm) [93, 96–98]. In PROVIDE-C, GPs will have no access to the trial intervention; therefore, the risk that GPs may implement some of the intervention to patients allocated to the control arm is small. At any rate, we will (a) measure the degree of potential contamination by capturing the number of patients in the control arm who receive video consultations from their GP and (b) consider the clustered structure of patients in practices as random effect in the regression analysis.

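### The per-protocol rule of at least three video consultations sets no criterion for controls; limited to the intervention arm, it compares patients selected after randomisation with all controls

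*Protocol article*

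**What the plan says.** Under Statistical methods, the primary analysis will "follow the intention-to-treat approach which includes all patients in the group they were allocated to by randomisation". The same paragraph adds: "In a sensitivity analysis, we will evaluate the per-protocol population". Membership of that set is then defined by a single condition: "only patients who will have participated in at least three video consultations (defined as engagement in video consultations) will be included". The rule is not confined to one arm, and nothing is said about which controls belong to the set.

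Other sections show what each arm is exposed to. Intervention integrity sets a "fixed dose of five video consultations of 50 min each for each patient", so the cut-off is three of five sessions. Comparison arm says: "Patients allocated to the control group will get the usual care provided by the GP". The Discussion says that the specialists "had no contact at all with participants from the control arm", and that contamination will be measured by "capturing the number of patients in the control arm who receive video consultations from their GP".

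The only adherence figures are from the feasibility trial, where "treatment retention (87.0%) and attendance at sessions (94.4%) was high" (Background and rationale). Neither figure is defined as attending at least three sessions. The Missing data section separately plans sensitivity analyses of the missing-data assumption.

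**The concern.** A per-protocol set needs an inclusion rule that patients in both arms can meet. This one is framed entirely in terms of a treatment that only one arm is offered. An analyst who follows the sentence has no control group. An analyst who departs from it must choose a comparison population that the protocol does not define, in a trial where patients and GPs know the allocation.

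The natural repair, keeping all controls and dropping intervention patients with fewer than three sessions, has its own problem. Patients who would not have engaged leave one arm, while their counterparts stay in the other. The contrast is then no longer protected by randomisation. It is nevertheless presented as a sensitivity analysis of the primary result, so agreement with the intention-to-treat estimate could be read as robustness, or a larger estimate as the effect in those treated. Neither reading is warranted.

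**Working it through.** **Inputs.** 320 patients allocated 1:1, so about 160 per arm. 20% loss leaves 160 × 0.80 = 128 per arm. Target 3 points (lower end of 3 to 5), SD 9, k = 0.35, two-sided 5% level. All are from Recruitment, Trial design or Sample size calculation. Engagement of 87% is an assumption: feasibility retention used as a proxy for three or more sessions.

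**Check against the plan.** Residual SD = 9 × √(1 − 0.35²) = 8.43. With 128 per arm, SE = 8.43 × √(1/128 + 1/128) = 1.05, and the power for 3 points is 0.81. This agrees with the stated 0.80. The plan gives no figure for the per-protocol set itself.

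**Literal reading.** Controls with at least three trial consultations: 0 of about 160 (0 of about 128 after loss). The group effect cannot be estimated. The one theoretical exception is a control with three or more video consultations from the GP. Keeping only such patients would retain exactly the contaminated controls.

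**Intervention-arm reading, precision.** 128 × 0.87 = 111 intervention patients face 128 controls. SE = 8.43 × √(1/111.4 + 1/128) = 1.09, and power is 0.78. At 70% engagement power is 0.73. Lost precision is minor.

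**Intervention-arm reading, bias.** Let p be the proportion who would engage if offered the intervention. By randomisation p is the same in both arms. Write I and C for mean improvement under intervention and control, with subscripts E (would engage) and N (would not). The per-protocol contrast is

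I_E − [p·C_E + (1 − p)·C_N] = (I_E − C_E) + (1 − p)·(C_E − C_N).

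The first term is the effect in engagers. The second is bias: (1 − p) times the prognostic gap under control. At p = 0.87 this is 0.13 × (C_E − C_N). An assumed prognostic gap of 2 to 4 points would give 0.26 to 0.52 points. No gap gives no bias, and a reversed gap reverses the sign. Non-engagers cannot be identified among controls, so the trial does not observe C_E − C_N.

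**Illustrative range.** Assume no true effect and a normal selection model with correlation ρ between engagement and improvement beyond what baseline severity explains. The protocol gives no value for ρ. Bias = ρ × φ(c)/p × 8.43, where c = Φ⁻¹(1 − p). Cells show spurious points and the false-positive rate.

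| Engagement p | ρ = 0.1 | ρ = 0.3 | ρ = 0.5 |
|---|---|---|---|
| 95% | 0.09; 5.1% | 0.27; 5.8% | 0.46; 7.1% |
| 87% | 0.20; 5.4% | 0.61; 8.7% | 1.02; 15.5% |
| 70% | 0.42; 6.5% | 1.26; 19.1% | 2.09; 43.8% |

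Negative ρ gives the same sizes in the other direction.

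**Instrumental alternative.** The complier effect is the intention-to-treat effect divided by p. For a 3-point effect this is 3/0.87 = 3.45 points, with SE of about 1.05/0.87 = 1.21. Estimate and SE are both divided by p, so their ratio, and hence the test of no effect, is essentially that of the intention-to-treat analysis.

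**The case against.** The strongest reply is that the parenthesis about engagement makes sense only for patients who are offered consultations. In context the rule is a minimum exposure for the intervention arm, and a pre-specified analysis plan is promised. This is persuasive as to intent. A reader might infer that the trial will end up with an empty control group; the documents do not support that as a realistic outcome. It does not rescue the rule, however. The protocol is not silent here: it fixes the set with a restrictive rule that cannot work for controls, and the intended reading carries the selection problem.

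A reader might also take 0.13 times the observed gap in improvement between engagers and non-engagers as the bias. That product is the shift from the intention-to-treat mean, and it is bias only so far as the gap is prognostic. If engagers gain 3.45 points from treatment, non-engagers gain none and prognosis is equal, the shift is 0.13 × 3.45 = 0.45 points with zero bias. The complier estimate moves by the same 0.45.

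Nor does the protocol show that the bias favours the intervention. Patients who stop early because they have improved would push it the other way. The planned covariates (baseline severity, history, physical health, chronic disease, gender, age) may reduce it but cannot be relied on to remove it. It would also be wrong to call this the only planned sensitivity analysis, since Missing data plans others; it is the only one described that concerns adherence.

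Finally, a complier analysis with a three-session cut-off assumes that one or two sessions do nothing. Specialist diagnostics is a core component, and the diagnostic report reaches the practice after the second consultation, so this assumption is doubtful. That objection stands and shapes the fix.

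**Conclusion.** The point holds as a badly fixed analysis set in a secondary role. As written, the rule leaves no comparison group. As probably meant, it gives a non-randomised contrast whose bias equals the non-engaging fraction times an unobserved prognostic gap.

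The tabulated range shows that the bias could be negligible (about 0.1 points with 95% engagement and weak correlation) or material (about 2 points with 70% engagement and strong correlation). These values rest on assumed correlations, and on 87.0% retention standing in for three or more sessions in the middle row. They illustrate sensitivity and are not an estimate for this trial.

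A reader might infer that the primary conclusion is at risk. It is not: the intention-to-treat analysis, the sample size and the primary test are untouched. The change is worth making because it is cheap and should be settled before outcomes are analysed.

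**What to change.** 1. State the criterion by arm: at least three video consultations in the intervention arm, all controls retained. Label the per-protocol result descriptive, and say that it is not a randomised comparison.

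2. Estimate the effect of adherence with a complier average causal effect analysis. Use randomised arm as the instrument, all randomised patients, and the covariates and general-practice effect of the primary model.

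3. State the exclusion restriction openly. Because fewer than three sessions may have an effect, repeat the analysis with another threshold, such as at least one session, or use the number of sessions attended.

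The cost is a few sentences in the analysis plan, one extra model and an interval about 1/0.87 = 1.15 times as wide as the intention-to-treat interval at 87% engagement. Session counts are already to be logged at the coordination centre (Intervention integrity) and reported per consultation (Process evaluation), so no new data are needed.

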### Sample size calculation

Based on the review of the existing evidence, especially of published, sufficiently powered RCTs in the areas of collaborative care [19] and integrated mental health [30, 33, 72] and opinion-seeking within the study team, we chose the absolute change in depressive and anxiety symptom severity on the continuous PHQ-ADS scale from screening (-t1) or, if the baseline assessment has been performed later than 28 days after screening, baseline (t0) to 6 months after baseline assessment (t2 = -t1 + 6 months or t2 = t0 + 6 months, respectively) to be the primary outcome of clinical relevance for patients and health policy makers. For this scale, a reduction of 3 to 5 points is considered clinically relevant and we expect a standard deviation of 9 points [44]. If this reduction is not achieved under the optimised study conditions, it is unlikely that even a minimal significant effect according to Cohen (*d* = 0.2) will be achieved under routine conditions [73]. Statistical tests will be performed at a two-sided significance level of *α* = .05 with a power of 1 − *β* = .80. With these parameters, a sample of *N'* = 292 was obtained. The sample size calculation was performed using PASS 16.0.3. Adjusted for a correlation parameter between baseline and the difference between baseline and post-assessment of *k* = 0.35 (for both intervention and control group) and taking into account 20% loss-to-follow-up (*m* = 0.20) (based on a large study on case management of depression by medical assistants in small German general practices [26]), the required sample size is *N* = (*N'* * (1 − *k*^2^))/(1 − *m*) = 314. For the sake of simplicity, the planning assumes *N* = 320 patients (see Fig. 1 for the study flowchart).

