#### Mental health specialists

We will recruit the MHS at the Institute for Psychotherapy, Heidelberg (HIP), which is a state-approved psychotherapeutic training facility at Heidelberg University Hospital. We will contact all lecturers licensed as psychotherapists and all trainees systematically using mailing-lists. All interested individuals will have to apply and will then be invited for a short interview. The final decisions on the participating psychotherapists will be made by mutual discussion and consensus formation in the study team. In total, we will recruit at least 30 psychotherapists or psychotherapy trainees, that is, psychologists in the advanced training period. Each general practice will permanently work together with one MHS only. MHS may participate in more than one recruitment wave. The MHS will participate in the trial as freelancers and will be paid per session according to the current fees for psychotherapy as reimbursed by the German statutory health insurance. For all MHS, expected time expenditure will be approximately 5 h per week (4 h for consultations, 1 h for supervision). All participating MHS will receive a 3-h introductory training, in which we will (1) obtain written informed consent, (2) outline the trial procedures, (3) familiarise MHS with the intervention by walking them through the manual and introducing the context of primary care, and (4) give a step-by-step instruction on conducting video consultations (e.g. room setup and videoconferencing platform,) to foster technical competency which is regarded as crucial for implementing telepsychiatry services [33].

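### The primary model's only random effect, general practice, does not represent differences between mental health specialists in the intervention arm; if specialists differ, the standard error is modestly too small and the sample size makes no allowance for it

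*Protocol article*

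**What the plan says.** Statistical methods specifies a mixed linear regression for the 6-month change in PHQ-ADS. Arm, baseline severity and five other baseline variables are fixed effects, and the single random term is "trial site (general practice) (random effect". The model carries the bracketed qualifier *robust*, which is not defined. The Discussion gives the same answer to clustering: the investigators will "consider the clustered structure of patients in practices as random effect in the regression analysis".

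Under Mental health specialists, the protocol states "Each general practice will permanently work together with one MHS only". It plans at least 30 MHS for 30 practices and lets an MHS take part in more than one recruitment wave. The Discussion adds that the specialists have no contact with control patients. Randomisation is individual, 1:1 and stratified by practice.

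The Sample size calculation assumes that "a reduction of 3 to 5 points is considered clinically relevant" and "we expect a standard deviation of 9 points". It sets a two-sided 5% level "with a power of 1 − *β* = .80". It then reports "With these parameters, a sample of *N'* = 292 was obtained", adjusted for a baseline correlation of 0.35 and 20% loss. No clustering term appears.

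**The concern.** Specialists may get different results. The protocol itself gives reasons: they range from licensed psychotherapists to advanced trainees, they may depart from the manual on their own judgement, and the working alliance is named as a core process. Patients treated by the same specialist would then have correlated outcomes, but only in the intervention arm.

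Write the outcome in practice j as a practice effect u_j for everyone, plus an MHS effect v_j for intervention patients only. The within-practice difference between arms is the treatment effect + v_j + error. The u_j drops out and v_j stays. A model with u_j alone has no place for v_j and treats most of it as independent patient-level noise. The standard error of the treatment effect is then too small.

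This is the trial's only confirmatory test, so its 5% level, its confidence interval and its planned power are what is at stake.

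**Working it through.** **Inputs from the protocol.** Difference 3 points (the lower end of the 3 to 5 range, and the only whole-point value in it that comes near the stated N'); SD 9; two-sided alpha 0.05; power 0.80; k = 0.35; loss 20%; 320 randomised; 30 practices. **Assumed:** the MHS ICC, meaning the share of residual variance in the intervention arm that is due to the specialist. The protocol gives none; the range 0 to 0.10 is used.

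**Step 1: the plan's own figures.** A two-sample comparison of 3 points with SD 9 needs 142 per arm (284) by the normal approximation, or 143 per arm (286) by the t test, against 292 stated. The printed formula gives 292 × (1 − 0.35²)/(1 − 0.20) = 292 × 0.8775/0.80 = 320.3; the stated 314 follows from 286 (313.7). These differences are under 3%, and the planned 320 covers both within rounding. No version needs a clustering term to reproduce it.

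**Step 2: starting point without clustering.** Residual SD = 9 × √0.8775 = 8.43. Analysed: 320 × 0.80 = 256, or 128 per arm. SE0 = 8.43 × √(2/128) = 1.054. Power = Φ(3/1.054 − 1.96) = 81.2%.

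**Step 3: add MHS clustering in the intervention arm only.** Patients per MHS: m = 128/30 = 4.27.

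- Design effect in that arm: DE = 1 + (m − 1) × ICC
- True SE = 8.43 × √((1 + DE)/128)
- Actual type I error when SE0 is used: 2 × [1 − Φ(1.96 × SE0/SE)]
- Power of a valid test: Φ(3/SE − 1.96)

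| MHS ICC (assumed) | DE | SE | SE/SE0 | Type I error | Power, 3 points | N randomised for 80% |
|---|---|---|---|---|---|---|
| 0 | 1.000 | 1.054 | 1.000 | 5.0% | 81.2% | 310 |
| 0.02 | 1.065 | 1.071 | 1.016 | 5.4% | 80.0% | 323 |
| 0.05 | 1.163 | 1.096 | 1.040 | 5.9% | 78.1% | 338 |
| 0.10 | 1.327 | 1.137 | 1.079 | 6.9% | 75.2% | 373 |

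**Step 4: fewer distinct specialists.** If only 20 MHS deliver the intervention (m = 6.4), type I error is 5.6%, 6.6% and 8.2%, and power 79.2%, 76.2% and 71.4%, at ICC 0.02, 0.05 and 0.10. The plan is for at least 30, so this is a stress case.

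**Step 5: does the practice intercept repair it?** The random-intercept model was fitted by REML to 4,000 simulated data sets per setting: 30 practices, one MHS each, 256 patients, total variance held fixed, no further covariates. Practice-clustered standard errors (factor 30/29, t on 29 df) were computed on the same fits. Monte Carlo error is about ±0.7 points around a 5% rate (1.96 × √(0.05 × 0.95/4,000)).

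| Practice ICC | MHS ICC | Empirical SE | Model SE | Type I, practice intercept | Type I, clustered SE | Power, clustered SE |
|---|---|---|---|---|---|---|
| 0 | 0 | 1.048 | 1.045 | 5.0% | 5.0% | 78.2% |
| 0 | 0.02 | 1.063 | 1.046 | 5.1% | 5.1% | 76.5% |
| 0 | 0.05 | 1.085 | 1.042 | 5.9% | 5.2% | 75.6% |
| 0 | 0.10 | 1.140 | 1.037 | 7.2% | 4.9% | 72.4% |
| 0.05 | 0 | 1.033 | 1.025 | 5.5% | 4.9% | 81.1% |
| 0.05 | 0.02 | 1.048 | 1.024 | 5.8% | 5.5% | 80.2% |
| 0.05 | 0.05 | 1.085 | 1.021 | 6.7% | 5.3% | 77.5% |
| 0.05 | 0.10 | 1.102 | 1.014 | 7.6% | 5.0% | 74.7% |

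The model SE does not rise with the MHS ICC although the true spread does, so the intercept does not repair the error. Clustered standard errors do.

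**The case against.** **The size rests on an assumed figure.** This stands. A reader might infer that the test is anti-conservative and the power overstated as matters of fact. The protocol gives no MHS ICC, and at 0.02 the effect is negligible: type I error 5.1% to 5.4% with no practice ICC, and power still 80%.

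**The clustering is not ignored.** This also stands in part. A reader might infer that the model disregards specialists altogether. With one MHS per practice, the cluster unit is largely the practice, which is in the model. What is missing is an effect specific to the intervention arm. A further level is needed only where one MHS serves several practices.

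**The word *robust* may already solve it.** If it means practice-clustered standard errors, the test is largely sound (4.9% to 5.5% in simulation). If it means resistance to outliers, it is not. The protocol does not say which, so this limits the claim without answering it. Intercept is likewise the natural reading of a site random effect, not the stated one.

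**The power loss has offsets.** The calculation credits only the baseline correlation. If practices explain outcome variance, the comparison gains: the planned model's simulated power with no MHS effect rose from 80.6% to 83.5% at a practice ICC of 0.05. The other covariates may add to this. The loss is therefore not certain.

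**This is SAP detail.** Degrees of freedom and coding usually are. But the protocol states the random-effects structure and offers it as its answer to clustering; an SAP that follows it faithfully inherits the gap.

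**Conclusion.** The point holds in conditional form. As naturally read, the stated random effect does not represent specialist variation in the intervention arm, and the sample size does not allow for it. If specialists differ, the standard error is about 2% to 8% too small for an MHS ICC of 0.02 to 0.10. Type I error is then about 5.4% to 7%, and valid power for 3 points about 80% to 75%. This rests on 30 MHS, 256 patients analysed, a residual SD of 8.43 and the assumed ICC. It is worse if fewer MHS serve several waves, and milder if practice or covariates explain outcome variance. It largely disappears as a problem of test validity if *robust* means practice-clustered standard errors. The documents do not support saying that the 5% level fails or that 80% power is lost outright. Severity: moderate; worth correcting, not a must-fix.

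**What to change.** Prespecify in the SAP, before the outcome data are analysed by arm:

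- An MHS random effect coded for intervention patients only, alongside the practice intercept. Give an MHS who works in several waves one identifier throughout. A random slope for arm within practice is the same term only while each MHS serves a single practice.
- Satterthwaite or Kenward-Roger degrees of freedom. The alternative is explicitly cluster-robust standard errors with a small-sample correction, clustered by MHS where one MHS serves several practices.
- What *robust* means.
- That this model stays primary whatever the variance estimate, including zero, so that the choice of model does not depend on the data.
- Power over an MHS ICC range of 0 to 0.10.

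The cost is about one line of model text and a short power table; the trial already holds practice and MHS assignments. The downside is a slightly wider interval and possible boundary fits with about four analysed patients per MHS. If specialists do not differ, the price is small: with practice-clustered errors, simulated power was 78.2% against 80.6% for the planned model (both ICCs zero).
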